### 2.9. Statistics 

#### 2.9.1. Sample Size Calculation 

Assuming a frequency of complications in the standard group of 60% and a decrease of 20% in the OFA group (minimal expected difference given the simultaneous consideration of several clinical events), 144 patients per group are required, i.e., a total of 288 patients with a power of 90% and an alpha risk (two-sided) of 5%. Considering the composite nature of the primary endpoint, we chose a power of 90%. Anticipating 10% non-evaluable data for the primary endpoint, we fixed the sample size to 320 patients, 160 in the OFA group and 160 in the control group (Supplementary Materials, consort Flow chart diagram). Sample size calculations were based on previously published studies on OFA in cardiac surgery and institutional databases [6,7].

#### 2.9.2. Data Analysis 

The main analysis will be conducted on an intention-to-treat basis and completed by a per-protocol (Supplementary Materials; flow chart diagram). The main conclusion of the trial will be on the intention-to-treat analysis only. The quantitative variables will be described by the mean ± standard deviation and the median [25–75% IQR] and qualitative variables will be described by their number (%). The characteristics of the two groups will be compared using the usual univariate test: Chi-square test or Fisher’s exact test for qualitative variables and Student’s or Wilcoxon’s test for quantitative variables, depending on the test conditions. 

Logistic regression adjusted on the stratification factors (centre and Euroscore 2) will be performed to analyse the effect of the type of anaesthesia on the rate of occurrence of postoperative complications.

The analysis of secondary endpoints will be performed using an ANOVA adjusted for stratification factors or the Wilcoxon test depending on the distribution of the variables for quantitative variables and a logistic regression adjusted for stratification factors for categorical variables. The time to extubation will be described and compared between the two groups using Kaplan–Meier curves and a log-rank test if the application conditions are met. If factors at inclusion appear unbalanced between the two groups, multivariate analyses will be performed including these factors in addition to the stratification factors. 

An intermediate analysis will be performed after the inclusion of 25% and 50% of patients. Thus, the safety of the trial (rate of serious adverse events between inclusion and POD 30), as well as the rate of occurrence of postoperative complications, will be described and analysed according to the treatment arm. These results will be submitted to the independent safety monitoring board, who will decide whether to stop the trial. The final statistical analyses will be performed using a significant level of 5%.

The intermediate analyses will use an alpha risk of 0.001 for each safety analysis of the trial, according to the method proposed by Peto–Haybittle, in order not to modify the significance level of the final main analysis. The statistical analysis is performed using SAS Software (version 9.4). 

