### 2.4. Randomisation 

Participants are randomised to receive either opioid-free anaesthesia (interventional group: OFA) or conventional anaesthesia with sufentanil (control group). This allocation is stratified by the centre and Euroscore 2. The 1:1 ratio randomisation is performed by an investigator not in charge of the patient on the day of the cardiac surgery to avoid bias, using the CleanWeb^TM^ software (V 176.1.0, Telemedicine Technologie SAS, Boulogne Billancourt, France), and this process is controlled by an identification using a password. The compliance of the data with the inclusion and non-inclusion criteria is checked a second time at this point. The treatment allocation algorithm of the randomisation was established by the Research Methodology Support Unit (USMR) of the Dijon Bourgogne University Hospital, which also offered technical support and keeps a confidential record of the full randomisation process.

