### 2.6. Data Collection 

The data are prospectively collected in an electronic CRF (e-CRF) created with CleanWeb software by a data manager. Demographic and surgical data are collected at the baseline visit. All patient-related data are anonymously prospectively noted in the e-CRF by a clinical research associate who is blind to the group assignment. Data consists of: gender, age, weight; size; ASA score; Euroscore 2; Apfel score; comorbidities; ventricular aneurysm; preoperative left ventricular ejection fraction (%); preoperative creatinine levels; drug consumption and the type of surgery; episodes of hypertension; hypotension; bradycardia and tachycardia; CPB time; aortic clamping time; duration of anaesthesia; biological assessment at the end of the bypass surgery; electrosystolic entrainment; total dose of propofol; sufentanil; lidocaine; ketamine; heparin; and protamine; total dose of insulin; total fluid balance; transfusion of red blood cells; tranexamic acid; catecholamine use (dose, type, duration); operative diuresis; veno-arterial ECMO; and intra-aortic counter pulsation balloon. Postoperative data comprise: time to extubation; complications; SOFA score; arterial lactates; catecholamine (type, dose, duration); total dose of insulin; total dose of morphine; postoperative pain episodes at rest and cough (VAS > 3) and the number of episodes of nausea–vomiting following 48 h after extubation; standard biological; additional analgesia. On discharge from the ICU, a QoR15 questionnaire is performed by a nurse who is blind to group assignment. 

Complications are prospectively noted from the day of operation until the 60th postoperative day (POD 60). A post-surgical consultation is performed at POD 30 and POD 60. This consultation could be replaced by a telephone call at POD 60 if it does not take place, but the information collected must correspond to the patient’s condition at POD 30. A telephone call is made at POD 90 to collect the vital status. The study scheme is presented in Figure 1.

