### 2.8. Outcomes 

The primary endpoint is a composite endpoint, which comprises the occurrence of at least one of the postoperative complications, defined according to European standards (6), within 30 days after surgery, as provided in Table 2. The complications are defined according to international recommendations (ESAIC, ESICM) [15,16]. 

The secondary endpoints are the occurrence of each type of serious complication within the first 30 postoperative days: total cumulative dose of morphine (in milligrams), the number of episodes of postoperative pain (VAS > 3) at rest and on coughing within 48 h of tracheal extubation, the post-surgical recovery by questionnaire (QoR15), the number of patients with an atrial rhythm disorder (arrhythmia due to atrial fibrillation or atrial flutter), the number of patients with an infectious episode (pneumonia, urinary tract infection, surgical site infection, or bacteraemia), the time to extubation of the resuscitation patient (hours), the number of episodes of postoperative nausea and vomiting in the first 48 h after extubation, the ICU stays in days, and the hospital stay in days.

For patients included at the hospital of Dijon, an additional blood sample specimen is constituted at different times: before the surgery, at the end of the CPB, 4 h after the CPB, on the first POD, and on the second POD.

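### The Apfel score is recorded but not prespecified for the nausea and vomiting endpoint; building it into whichever planned test is used is a small, free gain in precision

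*Protocol article*

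**What the plan says.** All references are to the protocol article.

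- Section 2.6 lists the score among the collected items: "Euroscore 2; Apfel score; comorbidities". It also states "Demographic and surgical data are collected at the baseline visit". The score sits among preoperative items and is read here as a baseline measurement. It is named nowhere else in the article.
- Section 2.7 makes nausea and vomiting, as side effects of morphine, a secondary objective. Section 2.8 measures them as "the number of episodes of postoperative nausea and vomiting in the first 48 h after extubation", which is a count.
- Section 2.9.2 sets the method for quantitative secondary endpoints: "The analysis of secondary endpoints will be performed using an ANOVA adjusted for stratification factors or the Wilcoxon test depending on the distribution". Categorical ones get "a logistic regression adjusted for stratification factors for categorical variables".
- Section 2.4 defines the factors: "This allocation is stratified by the centre and Euroscore 2".
- Section 2.9.2 leaves one route for other covariates: "If factors at inclusion appear unbalanced between the two groups, multivariate analyses will be performed including these factors in addition to the stratification factors".

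**The concern.** The article fixes the adjustment set for this endpoint and leaves out a recorded baseline score that is a natural candidate predictor of it. Centre and a cardiac operative-risk score were chosen for the randomisation, not because they predict nausea and vomiting. If many patients have no episode, the distribution rule may well select the Wilcoxon test, and as written that test drops even centre and Euroscore 2.

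The imbalance clause does not secure the gain. A prognostic covariate reduces residual variance even when the arms are balanced on it, and after randomisation they usually will be. A trigger based on observed imbalance would then leave the score out. It would also make the choice of model depend on the data.

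At stake is the precision of the comparison that would support a claim of fewer morphine-related side effects. Bias and false-positive risk are not at stake.

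**Working it through.** **The plan's own figures.** The article gives no power or event figure for this endpoint. The relevant input is 160 per arm, which section 2.9.1 derives from 144 per arm and 10% non-evaluable data: 144 / (1 − 0.10) = 160. The 144 itself is close to the normal-approximation sample size for 60% versus 40%, two-sided 5%, 90% power: 130 without and 140 with continuity correction, the latter within 3% of 144. Nothing below changes these figures.

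**Assumptions.** The article does not say what the Apfel score measures or how strongly. It is treated here as a risk score for nausea and vomiting. Its strength is varied from weak (rate × 1.3 per point) through moderate (× 1.6) to strong (× 2.0). In simulated overdispersed counts these correspond to a partial R² of about 2.6%, 6.9% and 12.2%.

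**Step 1, order of magnitude.** In a linear model the standard error is multiplied by √(1 − R²), and 160 per arm acts like 160 / (1 − R²). For an effect with 80% power unadjusted, the standardised signal is 1.960 + 0.842 = 2.802. Adjusted power is Φ(2.802 / √(1 − R²) − 1.960).

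| R² | SE ratio | Equivalent n per arm | Power |
|---|---|---|---|
| 0.026 | 0.987 | 164 | 81.0% |
| 0.069 | 0.965 | 172 | 82.7% |
| 0.122 | 0.937 | 182 | 84.8% |

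The gains are 1.0, 2.7 and 4.8 points. An R² of 0.20, beyond the strongest case simulated, would give 88.0%.

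**Step 2, ANOVA branch by simulation.** Gamma-Poisson counts, control mean 0.9, rate ratio 0.65, 160 per arm, 3,000 trials per setting.

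| Rate multiplier per point | Planned ANOVA | Planned ANOVA + Apfel |
|---|---|---|
| 1.3 | 67% | 67% |
| 1.6 | 62% | 65% |
| 2.0 | 55% | 62% |

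An independent rerun gave 67/62/55% and 68/65/61%, so the gain is about 0 to 6 points. Type I error with the score was 4.7 to 5.0%, and 4.8/4.2/5.0% in the rerun.

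**Step 3, Wilcoxon branch by simulation.** Gamma-Poisson counts under a separate set of assumptions: rate ratio 0.6, 160 per arm, 2,000 trials per setting.

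| Rate multiplier per point | Plain Wilcoxon | Stratified by Apfel (van Elteren) |
|---|---|---|
| 1.2 | 64.2% | 64.1% |
| 1.5 | 61.8% | 64.7% |
| 2.0 | 58.2% | 65.0% |

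The gain is 0, 3 and just under 7 points. Type I error was 3.8 to 5.2% for the plain test and 4.2 to 5.5% for the stratified one. The simulation error on each power figure is about 1 point (√(0.6 × 0.4 / 2,000) = 1.1%).

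**Step 4, would switching to the linear model be better?** In the step 2 model the plain Wilcoxon test has 58/54/50% power, so the ANOVA without the score already gains 9, 8 and 5 points. That gain comes from the change of test and depends on the model. Suppose instead that treatment mainly changes whether a patient has any episode (assumed 45% versus 30%), with a skewed count among those affected and the control mean kept near 0.9. Wilcoxon then has 75/75/70% power and ANOVA plus Apfel 46/45/44%, a loss of 29, 30 and 26 points. A separate check gave 70–78% against 43–48%. The documents do not say which model applies.

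**The case against.** The strongest reply is that nothing here is wrong. The planned tests hold their type I error, adjusting for the stratification factors matches the randomisation, and this is one of many secondary endpoints. An endpoint-specific covariate could also sit in a SAP that is not shown. All of this stands, except that the article is not silent: it states the covariates and the tests, so the point concerns a stated choice that can be improved. If the SAP already names the score, the point falls away.

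Four stronger readings are tempting, and the documents do not support them.

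- A reader might infer that the score is never used. Section 2.9.2 also compares the characteristics of the two groups and allows unbalanced inclusion factors into multivariate analyses. The score could enter either way.
- A reader might infer that a rank test cannot use the score. A stratified Wilcoxon test can.
- A reader might credit the score with the full 9 to 12 points that separate the plain Wilcoxon test from ANOVA plus Apfel in the step 2 model. Most of that difference comes from changing the test, except where prediction is strong; the score itself adds about 0 to 6.
- A reader might conclude that the linear model should become primary. Step 4 shows that this can cost far more power than the score can return.

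It is also fair to object that the predictive strength is assumed throughout. With a weak predictor the gain is practically nil.

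**Conclusion.** The point holds as a minor efficiency improvement. The score is recorded, the stated analysis does not prespecify it, and the imbalance clause does not secure the benefit.

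Under assumed weak to strong prediction (rate × 1.3 to 2.0 per point, 160 per arm), using it within the planned test adds about 0 to 6 points of power; the strongest Wilcoxon setting came out just under 7. Type I error stayed at about 4 to 6%, and no power was lost beyond simulation error. The size rests on assumed inputs because the documents give no event rate for nausea and vomiting and no measure of the score's predictive strength.

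A reader should not infer bias, an invalid test, or any effect on the primary endpoint or the sample size of 320.

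**What to change.** Before unblinding, add one sentence to the SAP. Suggested wording: *For the number of nausea and vomiting episodes, the Apfel score will be included whatever the observed balance between arms: as an additional covariate with centre and Euroscore 2 if the ANOVA is used, and as the stratification variable of a van Elteren test if the Wilcoxon test is used.*

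Keep the rank test available as the primary method for a skewed count, and do not replace it with the linear model. State how missing scores are handled and how sparsely filled score levels are pooled.

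The cost is that sentence and those two rules. No new data, visits or patients are needed.

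### The Wilcoxon fallback for quantitative secondary endpoints and the log-rank test for time to extubation leave out the randomisation strata that the plan's other models adjust for

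*Protocol article*

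**What the plan says.** Section 2.4 of the protocol article fixes the design: "This allocation is stratified by the centre and Euroscore 2", in a 1:1 ratio. Section 2.9.2 then sets the analysis:

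- **Primary endpoint:** logistic regression adjusted for centre and Euroscore 2.
- **Categorical secondary endpoints:** "a logistic regression adjusted for stratification factors for categorical variables".
- **Quantitative secondary endpoints:** "ANOVA adjusted for stratification factors or the Wilcoxon test depending on the distribution of the variables".
- **Time to extubation:** "Kaplan–Meier curves and a log-rank test if the application conditions are met".
- **If baseline factors look unbalanced:** "multivariate analyses will be performed including these factors in addition to the stratification factors".

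The quantitative secondary endpoints in section 2.8 are cumulative morphine dose, numbers of pain episodes and of nausea and vomiting episodes, the QoR15 recovery score, time to extubation, and "the ICU stays in days, and the hospital stay in days".

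**The concern.** The plan treats centre and Euroscore 2 as the standard adjustment set, then leaves them out of two branches. This is a stated method, not a detail left open: the article names each test and says where adjustment applies.

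The two branches may cover much of the secondary analysis. Doses, episode counts and lengths of stay are often skewed, so the Wilcoxon option is a likely route for several endpoints, although the article gives no distributions. Whether an endpoint is analysed by stratum would then depend on the shape of its data. Length of stay is also prominent: the abstract includes ICU and hospital stay in the main aim, and the hypothesis in section 1 repeats it.

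Stratified allocation balances the arms within strata. The true variance of the between-arm comparison therefore excludes the between-stratum part, but an unstratified test still counts that part as noise. Its standard error is too large, so it rejects less often than it should. At stake is the ability to detect real differences in secondary endpoints. False positives are not the issue.

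**Working it through.** **The plan's own figure.** Section 2.9.1 gives 144 per group for 60% versus 40%, 90% power and two-sided 5%. The pooled two-proportion formula gives (1.96·√0.50 + 1.2816·√0.48)² / 0.20² = 129.3, so 130 per group, or 140 with continuity correction, within 3% of 144. Then 288 / 0.9 = 320. The figure is reproduced closely enough. It concerns the primary endpoint only, and no power is stated for any secondary endpoint. What it supplies here is 160 patients per arm.

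**Inputs for the check.**
- From the article: 320 patients, 1:1, three centres, stratification by centre and Euroscore 2.
- Assumed, because the article does not give them: two Euroscore classes (six strata), a lognormal outcome, the size of the stratum effects and the treatment effect. No censoring was simulated for the log-rank test.

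**Expected size of the effect.** Let R² be the share of outcome variance explained by the strata. Under the null, the unstratified statistic has standard deviation of about √(1 − R²) instead of 1, so its true two-sided type I error is about 2·[1 − Φ(1.96 / √(1 − R²))]:
- R² = 0.10: 1.96/√0.90 = 2.066, giving 3.9%
- R² = 0.20: 1.96/√0.80 = 2.191, giving 2.8%
- R² = 0.30: 1.96/√0.70 = 2.343, giving 1.9%

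**Simulation A.** Total log-scale SD 1, treatment shift 0.32, 3,000 trials per scenario. Monte Carlo error is about 0.7 points on power and 0.4 points on a 5% error rate.

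| Variance explained by strata | Wilcoxon power, plain / stratified | Log-rank power, plain / stratified | True type I error, plain Wilcoxon / plain log-rank |
|---|---|---|---|
| 0% | 80.5 / 79.6 | 73.9 / 73.7 | 4.9 / 5.6 |
| 5% | 80.6 / 80.9 | 74.6 / 75.9 | 5.2 / 5.0 |
| 10% | 80.7 / 83.3 | 74.7 / 77.7 | 3.8 / 4.0 |
| 20% | 81.1 / 86.5 | 75.1 / 81.8 | 2.6 / 2.8 |
| 30% | 83.8 / 91.6 | 76.4 / 87.3 | 1.8 / 2.3 |

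The loss at 10%, 20% and 30% is 2.6, 5.4 and 7.8 points for Wilcoxon, and 3.0, 6.7 and 10.9 points for log-rank. The simulated error rates agree with the formula.

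**Simulation B.** Residual log-scale SD held at 0.7, treatment shift −0.22, stratum effects of 0.2, 0.35 and 0.5 per step, Wilcoxon only, 3,000 trials per scenario. With equal strata, the between-stratum variance is step² × (2/3 for three centres + 1/4 for two classes). For a step of 0.2 this is 0.0367, and 0.0367 / (0.0367 + 0.49) = 7%. The other steps give 19% and 32%.

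| Variance explained | Power, plain | Power, stratified | Loss | Type I error, plain |
|---|---|---|---|---|
| 7% | 77.7 | 79.4 | 1.7 | 3.8 |
| 19% | 70.9 | 78.1 | 7.2 | 3.2 |
| 32% | 64.9 | 77.7 | 12.8 | 2.0 |

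A holds the total variance fixed, so the stratified power rises. B holds the residual variance fixed, so the plain power falls. Both show the same gap. Across both simulations the stratified tests had null rejection rates of 4.3 to 6.1%, scattered around 5%.

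**The case against.** **The harm is limited and conditional.** The unstratified tests do not raise the false-positive rate, the primary analysis is adjusted, and no secondary endpoint carries a power claim. The larger losses need strata that explain a fifth to a third of the outcome variance, and the article does not show that they do. Section 2.5 says that anaesthesia, bypass and postoperative care are standardised, and section 2.5.3 standardises analgesia. That points to weaker centre effects, although circulatory support follows institutional protocols. All of this stands, and it limits the size of the point, but it does not explain why two branches differ from the others.

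**The imbalance clause may already cover it.** Multivariate analyses would include the stratification factors, but only if baseline factors appear unbalanced. Stratification makes imbalance on these two factors unlikely, so they would rarely trigger the clause themselves. It does show that the authors regard them as the default adjustment set.

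**Stratified rank tests are not free of cost.** They can lose efficiency with very small strata or when effects differ between strata, and the article gives no stratum sizes. With six assumed strata of no prognostic value, the cost was 0.9 points (Wilcoxon) and 0.2 points (log-rank), close to simulation error.

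**A stronger reading that does not hold.** A reader might infer that patients who die early are counted as having short, favourable stays, or that a death before extubation is simply censored. The article states neither. It gives the stays in days and names the tests, and naming a Wilcoxon or log-rank test does not fix how deaths are coded. A journal article commonly leaves that rule to the full protocol or analysis plan, so its silence is no finding.

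**Conclusion.** The point holds as an inconsistency within section 2.9.2 that can cost power on secondary endpoints. The plain Wilcoxon and log-rank tests are valid after stratified allocation, but they are conservative where the strata are prognostic.

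The loss is about 0 to 3 points of power if the strata explain up to 10% of outcome variance, and about 5 to 13 points at roughly 20 to 30%. At 10% and above, the true type I error falls to about 2 to 4%. These figures rest on assumed strata, outcome distribution and treatment effects, so they should be read as a range and not as a forecast for any one endpoint.

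Neither the primary analysis nor the main conclusion of the trial is affected. The change is worth making because it is cheap and brings these two tests into line with the rest of the plan.

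**What to change.** In section 2.9.2, or in the analysis plan before unblinding:

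- Replace the Wilcoxon fallback with the van Elteren (stratified Wilcoxon) test.
- Replace the log-rank test for time to extubation with a stratified log-rank test.
- Define the strata in both as the centre and the Euroscore 2 classes used at randomisation.
- If some centre-by-Euroscore cells could be very small, state in advance how they will be pooled.

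The cost is a change of wording and a few lines of code in SAS 9.4, which the article already names. No new data are needed. The loss of efficiency is negligible unless strata are very small.

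### Chance baseline imbalance selects the covariates of an additional adjusted model whose role is not stated; a short prognostic set named in advance would serve better

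*Protocol article*

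**What the plan says.** All the relevant text is in the protocol article, section 2.9.2 (Data Analysis).

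- **Baseline tests.** "The characteristics of the two groups will be compared using the usual univariate test", that is chi-square or Fisher for qualitative variables and Student or Wilcoxon for quantitative ones.
- **Main model.** In a paragraph of its own, the effect of anaesthesia type on postoperative complications is analysed by logistic regression adjusted for centre and Euroscore 2, the stratification factors of section 2.4.
- **Imbalance rule.** The next paragraph, which opens with the secondary endpoints, closes with: "If factors at inclusion appear unbalanced between the two groups, multivariate analyses will be performed including these factors in addition to the stratification factors".

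The section ties the trial's main conclusion to the intention-to-treat population. It does not say which model carries that conclusion once a further adjusted model exists.

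**The concern.** Allocation is randomised 1:1, so if randomisation was done properly every baseline difference between arms is chance. A covariate earns its place by predicting the outcome. The rule ignores that and picks covariates after the allocated data are seen.

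Two things are at stake. First, the trial may end with two logistic results for one endpoint, one of them with covariates nobody chose in advance, and no statement of which counts. In logistic regression the odds ratio also changes meaning when a prognostic covariate enters, so the two results would not estimate the same quantity. Second, prognostic variables already being collected could buy some precision if fixed in advance, and the rule does not deliver it.

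**Working it through.** **1. The plan's own figure.** Section 2.9.1 gives 60% in the control group, "a decrease of 20% in the OFA group", two-sided alpha 5% and power 90%, and concludes that "144 patients per group are required". I read the decrease as 20 points (60% v 40%), because a relative 20% (60% v 48%) would need 361 per arm.

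- Uncorrected: n = [1.960·√(2·0.5·0.5) + 1.282·√(0.6·0.4 + 0.4·0.6)]² / 0.2² = (1.386 + 0.888)² / 0.04 = 129.3, so 130 per arm.
- Continuity-corrected: (129.3/4)·[1 + √(1 + 4/(129.3·0.2))]² = 139.1, so 140 per arm, within 3% of 144.
- Allowance: "Anticipating 10% non-evaluable data for the primary endpoint" gives 288/(1 − 0.10) = 320, as stated.
- Power at 144 per arm without continuity correction: 92.8%.
- Planned marginal odds ratio: (0.4/0.6)/(0.6/0.4) = 0.44.

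The check below therefore uses 288 evaluable patients and marginal rates of 60% v 40%.

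**2. How often the rule would fire.** Section 2.6 lists 13 items from gender to type of surgery, or 12 without Euroscore 2, which is a stratification factor. With k independent factors tested at 5%, the chance of at least one flag is 1 − 0.95^k:

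- k = 12: 1 − 0.95^12 = 0.46
- k = 13: 1 − 0.95^13 = 0.49
- k = 25 (if comorbidities and drugs are split up): 1 − 0.95^25 = 0.72

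The 5% threshold and the independence are assumptions; the article gives neither.

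**3. Power, by simulation.** Set-up: 288 patients, 3 centres, Euroscore 2 split in two, stratified 1:1 allocation, and 15 independent baseline factors of which 4 are prognostic. A factor is flagged at p < 0.05, and marginal event rates are held at the stated values (8,000 trials per row). Covariate strength is assumed. Log-odds of 0.3, 0.5 and 0.7 per SD are odds ratios of e^0.3 = 1.35, e^0.5 = 1.65 and e^0.7 = 2.01.

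| Rates | Log-odds per SD | Stratification factors only | Imbalance rule | Fixed prognostic set |
|---|---|---|---|---|
| 60% v 40% | 0.3 | 93.5% | 93.3% | 95.2% |
| 60% v 40% | 0.5 | 93.0% | 93.6% | 96.3% |
| 60% v 40% | 0.7 | 93.1% | 93.7% | 97.7% |
| 60% v 45% | 0.3 | 73.7% | 74.0% | 76.8% |
| 60% v 45% | 0.5 | 73.1% | 73.0% | 80.7% |
| 60% v 45% | 0.7 | 74.0% | 74.5% | 85.0% |

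Monte Carlo standard error is about 0.2 to 0.5 points. Some factor was added in about 55% of trials, but a truly prognostic one in only about 19%.

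A separate run with 12 factors, 3 of them prognostic (4,000 trials per scenario), gave the lower end of the range. In the same column order, at log-odds 0.3 it gave 92.9 / 92.9 / 94.1% for 60% v 40% and 72.2 / 71.6 / 74.4% for 60% v 45%. At log-odds 0.59 (odds ratio 1.8) it gave 93.2 / 93.5 / 96.5% and 73.2 / 73.9 / 81.0%.

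**4. Type I error, same set-up as step 3, 60% in both arms (20,000 trials per scenario).** Here the flag was set at p < 0.05 or p < 0.10.

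- Stratification factors only: 5.0 to 5.2%
- Imbalance rule: 3.9 to 4.9%
- Fixed prognostic set: 4.9 to 5.5%
- Significance claimed if either the stratification-only or the rule-based result is significant: 5.6 to 6.0%

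**The case against.** The best defence is that the complications model is already fixed. It has its own paragraph, adjusting for stratification factors alone is a legitimate primary analysis, and the imbalance sentence closes a paragraph about secondary endpoints. This stands in part. Chance selects only an additional model. But the sentence does not restrict itself to secondary endpoints and does not call its result supportive, so the overlap with the primary analysis is left open. An analysis plan may settle this. It would, however, have to depart from a rule that the article states outright.

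A reader might infer more than the text supports, in four ways:

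- **That chance chooses the primary model.** It does not, for the reason just given.
- **That the rule biases the result or inflates type I error.** In the check it was slightly conservative when used alone. The inflation appears only if either result may be claimed.
- **That the trial has only about 80% power without covariates.** That follows from entering 0.44 as an odds ratio conditional on strong covariates. With three covariates at odds ratio 1.8 per SD, this means 60% v 43.5%, a marginal odds ratio of (0.435/0.565)/(0.6/0.4) = 0.51, which is not the planned effect.
- **That an odds ratio nearer 1 without the covariates is attenuation caused by the rule.** It is non-collapsibility; an unadjusted model shows the same value.

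Two further objections are fair. That imbalance will be judged by the univariate tests is an inference from their place in the same section. And the article does not itself show that creatinine, ejection fraction or type of surgery is prognostic; that is for the investigators to judge.

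**Conclusion.** The point holds in a limited form. The article states a data-driven rule for choosing the covariates of a further adjusted model and leaves that model's standing undefined. About half of properly randomised trials would trigger it (46 to 49% for 12 to 13 independent factors at 5%), mostly by adding factors with no bearing on outcome.

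The cost is not invalidity. Compared with stratification factors only, the rule changes power by less than one point either way in the runs shown. A fixed prognostic set raises it from about 93% to 94–98% at the planned effect, a gain of about 1 to 5 points, and by about 2 to 11 points at 60% v 45%. The error risk is modest, about 5.6 to 6.0%, and arises only if both results are open to be claimed.

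The power gains depend on covariate strengths that I assumed and on independent covariates. They shrink where a covariate overlaps with Euroscore 2. The planned sample size is not affected.

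**What to change.** - Delete the imbalance trigger and the baseline significance tests that would feed it. Present the baseline table descriptively.
- Before unblinding, and without regard to by-arm interim results, name one primary model: centre, Euroscore 2 and a short set of baseline covariates that the investigators judge prognostic. Preoperative creatinine, left ventricular ejection fraction and type of surgery are candidates, and section 2.6 already collects them.
- State that this model carries the conclusion, and label any other adjusted model, for any endpoint, as a sensitivity analysis.

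The cost is wording only, with no new data and no extra patients. The small downsides are a few more model parameters and a conditional odds ratio that differs in meaning from the one adjusted for stratification factors alone, which the report should say.
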